### *Baseline patient-reported questionnaire*

**Table 1** lists the patient reported outcome and experience measures to be collected by patient questionnaires. The content of the questionnaire was informed by a cross-mapping of recommended indicator sets [e.g. 28], and measures used in national surveys (e.g. GP Patient Survey, Health Survey for England, FCP evaluation) and previous research studies in the same population and setting. For evaluating social inequalities we used the PROGRESS-Plus framework[29,30] to inform our choice of individual- and area-level social stratifiers.

### *Brief monthly patient-reported questionnaires*

At months 1, 2, 4, and 5 following the index consultation the patient will be asked one question to report their pain intensity either using SMS text or postal questionnaire. Keele CTU has experience of using 2-way SMS text messages to collect outcome data in previous trials (Foster et al 2017,

Campbell et al 2016). The software development team within the CTU will support this data collection and will make use of an in-house bespoke database-driven Web-based system to manage the sending and receiving of SMS text messages. The participant will respond to Keele CTU via the third-party SMS provider. The CTU system will poll the third-party SMS provider for returned SMS text messages. On processing of returned SMS text messages, the system will import these into the study database and process the response according to the business logic defined in the project. Interception of the original message by a third party would reveal only what the questions were that were being asked, whilst interception of the response would only yield an alphanumeric string.

A telephone number will be provided to enable participants to contact Keele CTU if they have queries relating to the SMS text messaging during office hours.

#### *Follow-up patient-reported questionnaires*

The questionnaire will collect follow-up outcomes at 3 and 6 months including MSK health, healthcare utilisation, and work productivity and activity impairment.

### **6.3.4. Data linkage and extraction**

#### *Primary care electronic health record*

Information on comorbidities and MSK management, including those needed to address the primary objective, will be collected from the primary care electronic health record. This will include relevant prescription medications, referrals to other services (e.g., physiotherapy and secondary care specialists), referrals for investigations (e.g., radiographs, MRI/Computerized Tomography (CT) scans), sick certifications (fit notes), and further MSK-related primary care consultations.

#### *NHS Digital datasets*

Linkage to MSK-relevant hospital outpatient appointments, admissions, accident & emergency attendances (Hospital Episode Statistics) and diagnostic imaging (Diagnostic Imaging Dataset) outcomes held by NHS Digital will be sought through the Data Access Review Service (DARS).

#### *Healthcare provider characteristics*

Non-sensitive aggregate- and global-level data on general practices and MSK services (e.g. staffing levels, Quality and Outcomes Framework (QOF) performance) will be extracted from the freely available general practice workforce data (NHS Digital General Practice Data Hub), PHE National General Practice Profiles, and GP Patient Survey data. During site initiation visits with participating general practices we will clarify the current provision of selected recommended MSK services, e.g. First Contact Practitioner physiotherapists, vocational advice, stratified care for low back pain [31,32].

#### *Neighbourhood characteristics and assets*

Aggregate data on wider determinants of health (e.g. healthy diet, obesity, labour market, housing, built environment, journey time statistics) in local geographies (lower and middle super output areas, CCG, unitary authority) will be extracted from existing accessible sources (e.g. Strategic Health Asset Planning and Evaluation (SHAPE: health-related determinants); NOMIS (labour market statistics); Public Health England's Data Gateway and Local Health tools) and linked to individual-level datasets above to create multi-level data. This includes modelled estimates of the underlying population prevalence of MSK pain and disability from our previous PRELIM survey.

### **6.3.5. Withdrawal criteria**

Patients can withdraw from the patient-reported outcomes subcohort at any time by contacting and informing Keele CTU by telephone, email or letter. Withdrawal will mean no further reminders or invitations to complete questionnaires will be sent. Any information provided up to the point the participant withdraws will be anonymised and retained unless the request is made for data to be destroyed.

### **6.4. EHR-only processes of care**

For EHR-only processes of care objectives we will extract and analyse pseudonymised data from participating GP practices on relevant prescriptions (e.g. strong opioids), referrals, imaging, Fit Notes, and repeat GP visits among all eligible adult MSK consultants (defined in 5.2 above). Data extracted will be for the period July 2016 to Sep 2023. This retrospective period is required to provide a better understanding of changes over time in MSK care in participating GP practices (including whether between-practice differences in care are recent or more longstanding and pre-dating COVID; objective 2.2.3).

### **6.5. Risk Mitigation**

For individual patients who consult a participating general practice with a MSK pain condition, the potential risks from being asked to complete initial, three and six-month follow-up questionnaires plus a text or brief postal questionnaire about pain intensity in the intervening months, are considered to be very low. All questionnaire mailings will be sent within an enclosed envelope and include a pre-paid reply envelope to ensure patient confidentiality at all times. Questions are on the severity and nature of pain and other symptoms such as sleep disturbance and are therefore not considered a risk beyond minor inconvenience.

To ensure that consenting participants in the patient-reported outcomes sub-cohort are appropriately linked to the medical record data we will use NHS number as the key link variable. Furthermore, to check that the individual concerned is completing the questionnaire we will collect name of GP practice and date of birth as further validation items.

To ensure high response rates to the questionnaire, sensitive items (as judged by the Patient Advisory Group) have been removed from the questionnaire.

General practices will receive payment for the additional time required to set-up the study and retrospective searches they perform.

### **6.6. End of study**

The end of the study will be when the last participant completes the 6-month follow-up data collection process and all relevant medical record data have been collected.

## 7 STATISTICS AND DATA ANALYSIS

### 7.1. Sample size calculation

#### 7.1.1. Patient self-reported outcomes (primary objective 2.1.1.)

We anticipate from previous studies and discussions with GP colleagues that the level of practice engagement may wain if the recruitment period extends much beyond 3 months.

The median registered population size of general practices in North Staffordshire & Stoke-on-Trent is 7300. Assuming 80% are aged 18 and over and an annual consultation prevalence for musculoskeletal pain of 15%[33], then there will be 876 patients consulting for musculoskeletal pain on average per practice each year. Across 26 practices (2 per PCN), there will be 5694 eligible patients presenting in the 3-month recruitment period. Assuming a 25% response at baseline and 50% at follow-up, then there will be 1424 baseline responders (1139 (80%) consenting to further contact and record linkages) and 569 responders at 6-month follow-up (**Figure 1**).

**Figure 1.** Estimated number of patients recruited and followed up for the patient-reported outcomes subcohort (NB 3-month period of recruitment per practice).

[figure not shown]

The baseline response of 1424 will allow us to detect a difference of 3 or more points on the MSK-HQ (assuming standard deviation of 10) with 90% power at the 5% significance level for groups defined by a dichotomous covariate with prevalence of 10% (for example ethnicity: black, Asian, and ethnic minority patients vs white).

569 responders at 6-month follow-up will also allow us to detect a difference on the follow-up MSK-HQ of 3 or more points (assuming standard deviation of 10), with 80% power at the 5% significance level, for groups defined by a dichotomous covariate. This is based on a covariate with a prevalence of 10%, 2 follow-up time points (3m and 6m), adjustment for baseline MSK-HQ score, and assumed correlations of 0.5 between the two follow-up scores and between the follow-up and baseline

scores.[34] We will, however, use repeated measures multilevel models to ensure all patients responding at baseline can be included in the analysis.

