| Study Design                          | Observational Cohort Study                                                                                                                                                                                                                                                                                                                        |                                                                                                                                                                      |
| Study Intervention (where applicable) | N/A                                                                                                                                                                                                                                                                                                                                               |                                                                                                                                                                      |
| Study Participants                    | Adults aged 18+ years consulting general practice for a common musculoskeletal pain condition                                                                                                                                                                                                                                                     |                                                                                                                                                                      |
| Planned Sample Size                   | 
For patient-reported outcomes and experiences: 1,139 patients from 26 practices (completing a baseline questionnaire and consenting to further contact and individual record linkage)
 
For electronic health record (EHR)-only processes of care: 11,388+ patients from 26+ general practices (minimum of 150 patients per practice)
 |                                                                                                                                                                      |

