### 6.3.2. Informed consent

Potential participants in the patient-reported outcomes/experience subcohort will be asked for their consent to retain and analyse their questionnaire responses, to be contacted again in future for follow-up questionnaires for this study, to access relevant information from their medical records held at their general practice and by NHS Digital and link this to their questionnaire responses.

In both online and pen-and-paper questionnaire formats, informed consent from willing patients will be obtained at the end of baseline questionnaire completion. For the online questionnaire this will be e-consent through the secure web-based interface hosted by Keele University; for the pen-and-paper it will be written consent; for those opting for telephone-supported completion of the questionnaire, the administrator will obtain verbal consent. Consent is being sought after patients have completed the online questionnaire to ensure that patients know what data they are providing before agreeing to it, this is in line with how patients will be completing the paper questionnaire. If a patient stops the initial online questionnaire part way through and changes their mind before they consent, the data they have provided will be destroyed.

The consent section will include mandatory statements that potential participants must confirm that they agree to in order to participate in the study.

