As part of the baseline questionnaire, a minimal set of participant identifiable data will be collected in order to ensure an individual is correctly identified and that the right participant is identifiable for follow-up questionnaire completion. Both consent formats cannot be altered by the participant and will be dated either automatically by the web-based system for online completion or by the patient for manual completion. If the consent date is missing from the pen-and-paper consent form, the date the questionnaire was received will be added upon entry to the database by an administrator. If the patients' signature is missing from the pen-and-paper consent form, a completed consent form will be sought by following the incomplete consent procedure. Prior to seeking consent to study participation, all potential participants will have had the opportunity to access the Participant Information Sheet and contact a member of the study team. Patients who contact Keele CTU and provide consent over the telephone will be posted a hard copy of the Participant Information Sheet.

If potential participants decline the e-consent to take part in the study they will receive an onscreen notification thanking them for considering participation and explaining that they will not be contacted further. Those who do not consent to take part in the study will be notified all of their responses to the baseline questionnaire will be deleted.

We will also ask patients to provide either a) their mobile telephone number or email address (online questionnaire), b) their postal address and telephone contact number (postal questionnaire and from those completing over the telephone) for them to receive their follow-up questionnaires.

Patients completing the online consent will be given the option to obtain a copy of the consent form by emailing the study team.

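### Baseline power of 90% is computed on 1424 responders, but the planned sample of 1139 gives about 86% unless responders who decline contact or linkage can be analysed

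*Protocol*

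**What the plan says.** Section 7.1.1 builds the patient-reported sample in steps: "Assuming a 25% response at baseline and 50% at follow-up, then there will be 1424 baseline responders", followed by "1139 (80%) consenting to further contact and record linkages", and then 569 responders at 6 months. The baseline power statement uses the first of these counts: "The baseline response of 1424 will allow us to detect a difference of 3 or more points on the MSK-HQ". The stated power is 90% at the 5% level, with a standard deviation of 10 and a two-group characteristic of 10% prevalence, ethnicity being the example.

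The Study Summary gives the planned size of the patient-reported component as "1,139 patients from 26 practices (completing a baseline questionnaire and consenting to further contact and individual record linkage". Section 6.1 describes the subcohort as supplying linked questionnaire and record data for each person, and gives it the questions on variation in outcomes and experiences.

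Section 6.3.2 takes consent at the end of the baseline questionnaire. The consent section contains "mandatory statements that potential participants must confirm that they agree to in order to participate in the study", but the protocol does not list them. People who do not consent to take part are told that "all of their responses to the baseline questionnaire will be deleted".

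**The concern.** The power claim and the planned sample rest on different denominators. The baseline claim counts 1424 - 1139 = 285 people who are not in the sample size given in the Study Summary and who, if they decline linkage, are outside the linked subcohort of section 6.1. The follow-up claim in the same section does not count them, because 569 is half of 1139.

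The claim concerns the MSK-HQ, a main outcome of the first primary objective, and a contrast between a minority group and everyone else, which is the kind of comparison the study is set up to make. If the analysable baseline sample is 1139, the protocol promises more power than its own planned sample delivers.

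**Working it through.** **Inputs (section 7.1.1 unless noted).** Difference 3 points; standard deviation 10; prevalence 10%, so groups of 0.1N and 0.9N; significance level 5%; N = 1424 for the power statement; N = 1139 from the Study Summary. The protocol does not say whether the test is one- or two-sided. Two-sided is assumed here, because objective 2.1.1 asks for the direction of differences as well as their size.

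**The counts.**
- 5694 × 0.25 = 1423.5, rounded to 1424.
- 1423.5 × 0.80 = 1138.8, rounded to 1139.
- 1138.8 × 0.50 = 569.4, rounded to 569.

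The chain is consistent, and the consent loss is applied before the follow-up count.

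**Formula (normal approximation).** SE = 10 × √(1/(0.1N) + 1/(0.9N)); power = Φ(3/SE - 1.96); difference detectable with 90% power = (1.96 + 1.2816) × SE.

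**The plan's own figure, N = 1424 (142.4 v 1281.6).**
- SE = 0.883 and 3/SE = 3.40.
- Power = 92.5% (92.4% with the noncentral t distribution).
- Detectable difference at 90% power = 3.2416 × 0.883 = 2.86 points.

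The stated 90% is therefore not the exact value for 1424, but it is true as a minimum.

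**The planned sample, N = 1139 (113.9 v 1025.1).**
- SE = 0.988 and 3/SE = 3.04.
- Power = 85.9% (85.9% with the noncentral t distribution).
- Detectable difference at 90% power = 3.2416 × 0.988 = 3.20 points.

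**N needed for 90% power at 3 points.** (1.96 + 1.2816)² × 100 / (9 × 0.1 × 0.9) = 1297. The planned sample is 1297 - 1139 = 158 below this, so the margin that 1424 has over 90% does not absorb a 20% loss.

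**Sensitivity.**
- A one-sided 5% test would give 96.0% with 1424 and 91.8% with 1139.
- With 1139 and a two-sided test, 90% power for 3 points is reached once the prevalence is about 11.6%.

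**The case against.** The strongest reply is that the 80% is not consent to take part. It is consent to further contact and record linkage, and several places leave room for people who give baseline answers and nothing more. Section 6.3.2 lists keeping and analysing the answers, being contacted again, and access to records as separate items. The Plain English Summary presents later contact and linkage as things people may or may not agree to. Table 2 in section 7.2 counts all 1424 as participants completing the baseline questionnaire. On that reading section 7.1.1 is coherent: 1424 for a cross-sectional comparison at baseline, and the consenting base where follow-up is needed.

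This stands as a possible reading, and it rules out three stronger claims that a reader might infer.

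- *That the answers of all 285 will be deleted.* The deletion rule covers those who do not consent to take part. The protocol does not say that declining contact or linkage amounts to the same thing, since the mandatory statements are not listed.
- *That the baseline model must lose unlinked responders because it needs comorbidity from the record.* Section 6.3.4 says the record supplies information on comorbidities and management, "including those needed to address the primary objective, will be collected from the primary care electronic health record". Section 7.3.1.2 refers only to key case-mix variables and does not name comorbidity among them. Many candidates, such as age, sex, pain duration and ethnicity, are in the baseline questionnaire.
- *That clustering by practice lowers the power further by a known amount.* The protocol gives no intraclass correlation, and section 7.3.1.2 plans a multilevel model with patients nested within practices. A simple design effect for an analysis that ignores clustering does not describe that model.

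The reply does not remove the mismatch. The Study Summary still gives 1139 as the planned sample, and section 6.1 still assigns the outcome questions to linked data. Nothing in section 6.3.2 says that baseline-only participation is allowed.

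**Conclusion.** The concern holds, with moderate confidence, as a mismatch of denominators. The formula behind the power statement is not at fault. For the planned sample of 1139, power for a 3-point baseline difference is about 86% rather than 90%, and the difference detectable with 90% power is 3.2 points rather than 3. If some responders who decline contact or linkage can be analysed, the sample for an unlinked baseline comparison lies between 1139 and 1424, and the power between 85.9% and 92.5%.

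These figures assume a two-sided 5% test, a standard deviation of 10, a 10% prevalence and no allowance for clustering. The loss is modest and is specific to characteristics about as uncommon as 10%. The 6-month calculation already uses the consenting base and is not affected. The point is still worth correcting, because the protocol states a property for a primary objective that its planned sample does not deliver as written.

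**What to change.** Restate the baseline sentence in section 7.1.1 on 1139: 86% power for 3 points, or 90% power for 3.2 points, two-sided.

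If people who decline contact or linkage may still have their baseline answers kept and analysed, make three changes instead: say so in section 6.3.2, reconcile this with the 1139 in the Study Summary, and limit the 1424 figure to baseline analyses that need no linked data.

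Either way the cost is a few sentences. No recruitment target, questionnaire or analysis model has to change.

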### 7.1.2. EHR-only processes of care outcomes (primary objective 2.1.2)

Our study population will be all adults consulting for a relevant musculoskeletal pain condition over the study period. From the estimates in 7.1.1., we expect an average of 219 patients per practice over a 3-month period. This exceeds the 150 patients recommended as the minimum needed per service for assessing variation between providers using, for example, funnel plots.[35] Smaller practices (list size<5,000) are likely to fall below this target of 150 adult MSK pain consultants over a 3-month period. We therefore intend to extract pseudonymised, record-based outcomes for eligible adults consulting for a MSK pain condition in each practice over 6-month intervals. This will enable practices with list sizes as small as 2500 to meet the target of 150 patients. For 26 practices, this yields a total sample size of roughly 11,388. However, for this component of the study, where the burden on general practices is very low, we will extend the invitation to participate to all general practices in North Staffordshire & Stoke-on-Trent using the EMIS clinical IT system and, if necessary, to other eligible and interested practices in the West Midlands.

## 7.2. Planned recruitment rate

The rate of patient recruitment for the patient reported outcomes per practice is detailed above. The overall rate of patient recruitment to this study will depend on when each practice begins patient recruitment. Due to practice circumstances, CTU and CRN capacity, we anticipate a staggered start for practices over a 3-month period (**Table 2**).

**Table 2.** Planned recruitment rate, by month

| Month                                                                                                                 | 1   | 2    | 3    | 4    | 5    | 6 |
|-----------------------------------------------------------------------------------------------------------------------|-----|------|------|------|------|---|
| No. of GP practices recruiting                                                                                        | 8   | 17   | 26   | 18   | 9    | - |
| Cumulative eligible adult MSK consultants                                                                             | 584 | 1825 | 3723 | 5037 | 5694 | - |
| Cumulative no. of participants completing baseline questionnaire a                                         | 146 | 456  | 931  | 1259 | 1424 | - |
| a Does not account for lag between consultation and completion of baseline questionnaire (est. average 2w) |     |      |      |      |      |   |

